### Sample size

The sample size of 205 PDAC cases was based on a target sensitivity of 85%, with 7% precision and 80% power, informed by pilot data on 132 patients.^10^ We aim to recruit the same number of each type of control, totalling 615 participants with complete data. Allowing for 20% attrition due to loss of samples, we will recruit 771 participants, which includes at least 256 with cancer.

Riley *et al*^11^ also recommend ensuring that the sample size achieves small mean absolute prediction error (MAPE), defined as the mean absolute difference between predicted and observed outcomes (cancer=1, no cancer=0), and large variation explained by the CPM, measured by Cox-Snell R^2^, which ranges from 0 for no predictive value to 1 for perfect prediction. Additionally, the area under the receiver-operating curve (AUC) provides an estimate of the ability of the CPM to discriminate between cancer and non-cancer cases. The resulting CPM based on 615 participants will have an MAPE of 0.048, estimate cancer incidence with precision 0.088, and achieve a minimum Cox-Snell R^2^ of 0.431 based on forty predictors. The SE in the AUC achieved by the CPM will be 0.016, based on an AUC of 0.86.

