#### Developing and reporting the CPM

Initially, relationships between candidate VOCs and the presence of PDAC will be explored using univariate logistic regression models, including linear, polynomial and cubic splines.

Given the large number of initial variables, a screening step will be undertaken to identify the most promising candidate VOCs for inclusion in statistical models, with approximately the top 50 being retained. To develop the CPM, a logistic regression model with variable selection and importance assessment techniques will be fitted. Robust variable selection methods will be used, specifically the least absolute shrinkage and selection operator (LASSO) and elastic net. LASSO aids in selecting a more parsimonious model by shrinking less important predictor coefficients to zero, while elastic net combines the penalties of LASSO and Ridge regression, effectively managing correlated predictors.^14^

Elastic net is particularly beneficial when dealing with highly correlated variables, as it can select groups of related predictors, making it well-suited for multivariate datasets like VOC profiles. The best-performing model, determined through nested cross-validation (CV), will be advanced for further analysis.

In addition to the statistical methods, random forest and deep neural networks (DNNs) will be used to enhance model predictions. Random forest constructs multiple decision trees from different data subsets and combines their predictions, handling complex, non-linear relationships in the VOC data and identifying key VOCs that predict PDAC. DNNs, capable of capturing patterns in high-dimensional data, will be employed to model non-linear relationships in the VOC data. The DNN architecture will include a designed number of hidden layers and neurons, with regularisation techniques like dropout applied to prevent overfitting.

The model will be enhanced by assessing the additional diagnostic value of patient and clinical features (eg, family history of cancer, presenting symptoms), potentially improving its predictive power and clinical applicability.

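### The Cox-Snell R² of 0.431 is what 40 predictors would require at n = 615, not what the model will achieve; the protocol's AUC of 0.86 implies about 0.34, and about 50 VOCs, not 40, enter modelling

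*Protocol article*

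**What the plan says.** The Sample size section (Protocol article) derives "The sample size of 205 PDAC cases" from a sensitivity target and sets the total with "We aim to recruit the same number of each type of control, totalling 615 participants with complete data". It then turns to guidance on sample size for prediction models. It describes Cox-Snell R² as a measure "which ranges from 0 for no predictive value to 1 for perfect prediction". It says that "The resulting CPM based on 615 participants" will achieve, among other things, a minimum Cox-Snell R² "of 0.431 based on forty predictors". The next sentence gives a standard error for the AUC, "based on an AUC of 0.86". No anticipated R² and no target shrinkage are stated.

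The section Developing and reporting the CPM explores each VOC singly, "including linear, polynomial and cubic splines". It then screens a large initial set of variables, "with approximately the top 50 being retained", fits LASSO and elastic net logistic models, and afterwards assesses what patient and clinical features add. The same section takes forward predictors selected in at least half of the bootstrap runs and reports coefficients with standard errors and odds ratios with confidence intervals.

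**The concern.** A sample size cannot make a model achieve a given R². How much variation the VOCs explain depends on the biology and the assay; the sample size governs how much of the apparent fit is lost in new patients. In the cited kind of calculation, R² is an assumed input, and a minimum R² is the smallest value at which the chosen n is large enough. Printed as an outcome, it reads as reassurance when it is a condition still to be met.

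Two other statements bear on whether it is met: the assumed AUC of 0.86, and the number of candidate predictors, which is 40 in one section and about 50 in the other. If the condition fails, an unpenalised model fitted to these data may give predicted risks that are too extreme. This matters because the section Derivation of diagnostic rules sets referral, review and discharge thresholds, and computes net benefit, from those predicted risks.

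**Working it through.** **Inputs from the protocol.** n = 615 with complete data, 205 of them cases, so the case fraction is 205/615 = 1/3; P = 40 predictors; stated R² 0.431; AUC 0.86 (all from Sample size); about 50 VOCs retained (Developing and reporting the CPM).

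**Inputs assumed.** Target shrinkage S = 0.9, inferred below; a roughly normal linear predictor, needed to convert an AUC into an R².

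**1. Reproducing 0.431.** The shrinkage criterion is n = P / [(S − 1) ln(1 − R²/S)]. Solved for R²:

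R² = S{1 − exp[−P / (n(1 − S))]} = 0.9 × [1 − exp(−40/61.5)] = 0.430.

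With n = 614 it is 0.431. Other targets do not fit: S = 0.85 gives 0.299 and S = 0.95 gives 0.691. Nor do neighbouring counts: P = 39 gives 0.423 and P = 41 gives 0.438. So 0.431 is the R² required for 40 parameters at shrinkage 0.9.

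**2. Scale of R².** At a case fraction of 1/3 the maximum Cox-Snell R² is

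1 − exp{2[(1/3)ln(1/3) + (2/3)ln(2/3)]} = 0.72.

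It cannot reach 1 here. The required value is 0.431/0.72 = 60% of the maximum.

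**3. R² implied by AUC 0.86.**

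| Assumption | Cox-Snell R² |
|---|---|
| Normal in cases and controls, equal variance | 0.337 |
| Single normal linear predictor, calibrated logistic model | 0.337 |
| Case SD 0.7 to 1.5 times control SD | 0.335 to 0.371 |
| AUC 0.91 instead (equal variance) | 0.433 |

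An R² of 0.431 thus needs an AUC of about 0.91.

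**4. Sample size needed for 40 parameters at S = 0.9.** With R² = 0.337:

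n = 40 / [−0.1 × ln(1 − 0.337/0.9)] ≈ 852.

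With the most favourable value in the unequal-variance range, R² = 0.371, the same formula gives about 753. Both exceed 615.

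**5. Expected shrinkage at n = 615.** Solving 615 = P / [(S − 1) ln(1 − R²/S)] for S with R² = 0.337:

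| Parameters | R² required for S = 0.9 | n needed for S = 0.9 | Formula shrinkage at 615 |
|---|---|---|---|
| 40 | 0.430 | 852 | 0.87 |
| 50 | 0.501 | 1,065 | 0.84 |

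The criterion counts candidates examined. The 50 VOCs are themselves chosen from a larger pool and clinical features follow, so 0.84 is an upper bound if screening uses the outcome.

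**6. Simulation.** Unpenalised logistic models with all parameters kept, 205 cases and 410 controls, true AUC 0.86 with normal predictors, gave mean calibration slopes of about 0.75 with 40 parameters and 0.69 with 50. These are lower than the formula values, so the formula is optimistic in this setting. They describe unpenalised fits only.

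**The case against.** The strongest reply is that the Cox-Snell figure does not carry the design. The 205 cases, and hence 615, come from the sensitivity target, and the prediction-model checks are added afterwards. The word minimum partly signals a threshold, so the fault is largely one of wording. This stands as a limit on the consequence, but the sentence still promises a value that its neighbour does not support.

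The calculation also rests on two things the protocol does not state. S = 0.9 is inferred, although no other value tried reproduces the figure. AUC alone does not fix R²: an extreme ROC shape with 72% of cases perfectly separated would give 0.51 at AUC 0.86. Nothing in the document suggests such a shape, but the assumption has to be declared. The protocol itself uses 0.86 only for the standard error of the AUC.

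A reader might go further in four ways that the document does not support.

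- *That predicted risks will be too extreme.* The simulated slopes are from unpenalised fits. LASSO and elastic net are planned and would reduce the problem, alongside nested cross-validation, bootstrap optimism and calibration plots. But the reporting of standard errors and odds ratios, and the fitting of models on a final predictor set under Outlier and missing data considerations, leave an unpenalised refit open. The text supports may, not will.
- *That the protocol claims little overfitting at 615.* It makes no such statement.
- *That splines and polynomials multiply the 50 VOCs.* They are mentioned only for the univariate exploration.
- *That 615 therefore supports about 28 parameters.* Inverting the formula gives that number, but the simulated unpenalised slope at 28 is only about 0.82. If screening uses the outcome, shortening the screened list also does not reduce the candidates examined to 28.

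**Conclusion.** The statement is wrong as written and should be corrected. The figure of 0.431 is a requirement under an inferred shrinkage target of 0.9. Assuming a roughly normal linear predictor, the protocol's own AUC corresponds to about 0.34, and at most 0.37 over the unequal-variance range examined, so the criterion is not met for 40 parameters at 615. The shortfall in complete participants is about 237 (852 − 615), or about 138 (753 − 615) at the favourable end. The count of 40 also disagrees with the roughly 50 VOCs carried into modelling, and the stated upper limit of 1 for R² should be 0.72.

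The arithmetic is firm given the two stated assumptions. The effect on the final model is less certain, because it depends on whether the penalised coefficients are kept. The primary justification of the sample size, by sensitivity, is not affected by this point.

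**What to change.** In Sample size:

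- Relabel 0.431 as the Cox-Snell R² required for an expected shrinkage of 0.9 with 40 parameters and 615 participants, and state the 0.9.
- Give the R² implied by the AUC of 0.86 (about 0.34, maximum 0.72 at one third cases) together with the distributional assumption behind it, and correct the 0-to-1 range.
- State that the criterion is not met at 615, and give the expected shrinkage (about 0.87 for 40 parameters, 0.84 for 50) as an upper bound, because screening adds candidates.

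Use one candidate count in Sample size and in Developing and reporting the CPM, including the clinical features. Do not replace the present claim with a statement that 615 supports 28 parameters.

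Specify that the final model keeps its penalised coefficients, or has the bootstrap shrinkage applied, with no unpenalised refit before the thresholds in Derivation of diagnostic rules are set.

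The cost is a correction to the text and a less favourable stated figure. No extra patients are needed.

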### Participant recruitment

Participants will be identified as potentially eligible for inclusion in VAPOR 1 by their direct care teams at participating NHS hospital sites and diabetes education centres across England, Scotland and Wales. PDAC participants will be identified through HepatoPancreaticoBiliary multidisciplinary team meetings in addition to operating theatre, endoscopy, imaging or outpatient clinic lists, or emergency presentations to the hospital. Patients with new-onset diabetes mellitus will be identified by direct care teams, including diabetes specialist nurses and referrals from general practice. Those with chronic pancreatitis will be identified from hospital outpatient clinic, imaging or endoscopy lists and will be confirmed by imaging within no strict timeframe. Healthy controls will be identified through review of operating theatre, endoscopy, imaging and outpatient clinic lists, ensuring potential participants have undergone imaging confirming a normal pancreas within the last year. Patients in other research studies are eligible if requisite consent is given and the study has ethical approval. Potential participants will be approached about study participation by a member of their local VAPOR 1 research team. If they are interested in participating, they will be provided with the participant information sheet for the study. Where possible, participants will be given at least 24 hours to decide whether or not to take part in this study. In all instances, participants will be given the maximum time available to decide whether to take part in this study. Participant recruitment visits will be aligned with planned hospital appointments, investigations or procedures wherever possible. Fully informed written consent will be obtained prior to obtaining their breath sample, which is collected as two breath samples given at one time point.

### Breath collection

All research team members who will be recruiting participants are trained in breath collection by an approved member of the Imperial College London VOC Laboratory. Participants are asked to fast, apart from water, for a minimum of 6 hours prior to breath collection. For participants undergoing surgery or a procedure, breath samples must be obtained preoperatively, prior to administration of sedation, anaesthetic or other pharmacological agents. After providing written informed consent, the research team will collect demographics, tumour characteristics and medical history from the participant (see online supplemental table 1). They will then be asked to rinse their mouth with water and provide breath samples by exhaling into two single-use breath collection bags via a mouthpiece that is subsequently sealed. A bespoke pump developed in-house will collect breath from each bag onto two thermal desorption (TD) tubes for 4 min, at a rate of 200 mL/min,^12^ resulting in four TD tubes per patient, each containing 800 mL of breath. Room air samples will also be collected onto two additional TD tubes to control for potential background environmental contamination. All TD tubes are transported at room temperature to the Imperial College London VOC Laboratory. Other factors that could affect VOC profiles, such as dietary intake and environmental exposures, including smoking, have been considered in the study design. As a result, participants are requested to fast for 6 hours prior to breath collection, with the time the participant last ate and drank recorded as well as the last cigarette and alcohol intake, if any. Figure 1 shows the study procedures before, during and after recruitment.

**Figure 1 F1:**
[figure not shown]
A flowchart demonstrating VAPOR 1 study procedures before, during and after recruitment. VAPOR 1, Volatile organic compound Assessment in Pancreatic ductal adenOcaRcinoma; VOC, volatile organic compound.

### VOC analysis

Breath and room air samples will be analysed at the Imperial College London VOC Laboratory in accordance with established standard operating procedures (SOPs). On receipt of the samples, the TD tubes are purged with dry, inert gas to remove moisture and stored at −80°C until analysed. Volatolomic profiling is undertaken using thermal desorption–gas chromatography–time of flight–mass spectrometry (TD-GC-ToF-MS) instruments (Markes TD100-XR, Agilent 6890, BenchTOF2, SepSolve, UK) equipped with either a Rxi-624SilMS column (RESTEK, UK) for the ‘mid-polar’ method or Stabilwax-DA column (RESTEK) for the ‘polar’ method. Two breath samples and a room air sample will be analysed using the ‘mid-polar’ method and the remaining breath and room air samples will be analysed using the ‘polar’ method. For further identification of VOCs, samples can be recollected and analysed by two-dimensional TD-GCxGC-ToF-MS (Markes TD100-XR, Agilent 7890, Sepsolve modulator, BenchTOF2, SepSolve).

Deuterated internal and surrogate standards are added to each TD tube to account for variation in sampling and analysis. Regular system suitability checks and quality control samples are run on each gas chromatography–mass spectrometry (GC-MS) instrument to ensure the validity of results. The acquired spectra will be compared against the National Institute of Standards and Technology mass spectral library by matching mass spectra-retention indices and authentic standards for chemical verification of compounds. Data will be extracted, pre-processed and quality controlled using ChromSpace (Markes) and in-house scripts.

Scientists analysing the GC-MS data will have access to pseudonymised data. All study data will be collected according to the Data Protection Act 2018 and in line with the General Data Protection Regulation (GDPR). To ensure data minimisation, the data that will be collected has been carefully decided by the researchers and statisticians for the study to ensure only the relevant and suitable data is collected for the intended purposes. Study data that leave the local clinical/research teams will be converted to a linked pseudonymised format and will be stored electronically within an online password-protected database. Access to the data will be restricted to authorised users and will be controlled and stored in accordance with the Data Protection Act 2018 and GDPR. No identifiable patient data will leave the local clinical/research team. Study data transferred to external organisations will be sent in a pseudonymised format and will be transferred via Imperial College’s approved secure data transfer system. Data Sharing Agreements will be in place prior to any data sharing.

### Statistical analysis

The number of patients recruited into the VAPOR 1 study, breath samples provided, and samples successfully processed and analysed will be reported in a flow diagram. The number (%) of cases where there was failure to provide breath samples, quality control failures, exclusion from the study following recruitment or withdrawals of informed consent will be reported, along with summaries of baseline characteristics by study group. Missing data will be reported for each variable. We will report all findings from the study according to the Transparent Reporting of a multivariable prediction model for Individual Prognosis or Diagnosis Statement.^13^

#### Developing and reporting the CPM

Initially, relationships between candidate VOCs and the presence of PDAC will be explored using univariate logistic regression models, including linear, polynomial and cubic splines.

Given the large number of initial variables, a screening step will be undertaken to identify the most promising candidate VOCs for inclusion in statistical models, with approximately the top 50 being retained. To develop the CPM, a logistic regression model with variable selection and importance assessment techniques will be fitted. Robust variable selection methods will be used, specifically the least absolute shrinkage and selection operator (LASSO) and elastic net. LASSO aids in selecting a more parsimonious model by shrinking less important predictor coefficients to zero, while elastic net combines the penalties of LASSO and Ridge regression, effectively managing correlated predictors.^14^

Elastic net is particularly beneficial when dealing with highly correlated variables, as it can select groups of related predictors, making it well-suited for multivariate datasets like VOC profiles. The best-performing model, determined through nested cross-validation (CV), will be advanced for further analysis.

In addition to the statistical methods, random forest and deep neural networks (DNNs) will be used to enhance model predictions. Random forest constructs multiple decision trees from different data subsets and combines their predictions, handling complex, non-linear relationships in the VOC data and identifying key VOCs that predict PDAC. DNNs, capable of capturing patterns in high-dimensional data, will be employed to model non-linear relationships in the VOC data. The DNN architecture will include a designed number of hidden layers and neurons, with regularisation techniques like dropout applied to prevent overfitting.

The model will be enhanced by assessing the additional diagnostic value of patient and clinical features (eg, family history of cancer, presenting symptoms), potentially improving its predictive power and clinical applicability.

A 10-fold CV will be used for internal validation of statistical and machine learning models. Nested CV will be applied to best identify the penalty terms in LASSO and elastic net models, as well as to fine-tune the hyperparameters in random forest and DNNs, reducing the risk of overfitting across all models. For each fold in the internal CV, the sensitivity, AUC, precision-recall AUC and the MAPE will be calculated and summarised by median (IQR) values across folds. Apparent performance with 95% CIs and optimism will be calculated by 100 bootstrap resamples. Predictors chosen in ≥50% bootstrapped selection routines will be taken forward.

For the final model, bias-corrected ROC (receiver operating characteristic) curves and calibration plots will be provided. All model coefficients with SEs, and ORs with 95% CIs will be reported.

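### The top-50 VOC screen is not placed inside the cross-validation folds or bootstrap resamples; run once on all participants, it biases the internally validated AUC upward by an amount that depends on the unstated number of VOCs

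*Protocol article*

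**What the plan says.** The section on developing and reporting the clinical prediction model (CPM) in the protocol article gives an order of work.

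- First, "Initially, relationships between candidate VOCs and the presence of PDAC will be explored using univariate logistic regression models", with linear, polynomial and spline forms.
- Next, because there are many variables, "a screening step will be undertaken to identify the most promising candidate VOCs for inclusion in statistical models". Roughly 50 are kept. Neither the ranking criterion nor the number of VOCs entering the screen is given.
- Then LASSO and elastic net logistic models are fitted, and nested CV decides which goes forward. Random forest and deep neural networks (DNNs) are added.
- Internal validation is by 10-fold CV. On the inner loop the text says "Nested CV will be applied to best identify the penalty terms in LASSO and elastic net models", and adds hyperparameters of the machine learning models.
- Apparent performance and optimism come from 100 bootstrap resamples, and "Predictors chosen in ≥50% bootstrapped selection routines will be taken forward". Bias-corrected ROC curves are planned for the final model.

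The article does not say whether the screen is repeated within folds or resamples.

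**The concern.** A held-out fold gives a fair test only if it played no part in building the model it tests. Choosing 50 VOCs from a long list by their association with PDAC is probably the most outcome-dependent step in the pipeline, and it is the step that the described scope of nested CV leaves out. If it is done once on all participants, each held-out fold has already helped pick the predictors. Some of the 50 will be chance associations that hold in those same participants and not in new ones.

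The bootstrap does not repair this if resampling starts from the 50 VOCs already chosen. It then measures the optimism of fitting within the 50, not the optimism of having selected them.

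The stated objective is to develop and internally validate the model, and the article describes no external validation. The referral thresholds and decision curves are built on probabilities from the same model, so optimism in its validation would carry into the assessment of clinical utility.

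**Working it through.** **Inputs from the Sample size section.** The number of cases is set by this sentence: "The sample size of 205 PDAC cases was based on a target sensitivity of 85%, with 7% precision and 80% power". Two equally large control groups bring the complete-data total to 615. On losses, the section says "Allowing for 20% attrition due to loss of samples, we will recruit 771 participants". The model is to "achieve a minimum Cox-Snell R^2^ of 0.431 based on forty predictors". The planned AUC is 0.86 with standard error (SE) 0.016.

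**Reproducing the plan's figures.**
- Cases: n = (z0.975 + z0.80)² × p(1 − p) / d² = (1.960 + 0.842)² × 0.85 × 0.15 / 0.07² = 204.2, so 205. Two-sided alpha of 0.05 is assumed because none is stated.
- Recruitment: 205 / 0.8 = 256.25, so 257 per group, and 3 × 257 = 771.
- Total: with 40 predictors, Cox-Snell R² of 0.431 and an assumed shrinkage of 0.9, n = 40 / [(0.9 − 1) × ln(1 − 0.431/0.9)] = 613.7, so 614 against 615 planned.

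The analysis set for the check is therefore 205 cases and 410 controls.

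**Main simulation.** The number of VOCs is assumed, from 100 to 2000. VOCs are independent and Gaussian. In the signal settings, k informative VOCs are shifted in cases by δ = √2 × Φ⁻¹(A) / √k, so that the best attainable AUC is A. The top 50 are taken by absolute univariate t. LASSO logistic regression is fitted with its penalty tuned by inner CV, and the median AUC over 10 outer folds is recorded. The true AUC is that of the full-data model in 3000 new subjects. There are 10 replicates per setting.

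Each cell gives the CV AUC with one screen on all data / AUC in new subjects / bias (bias from unrounded values).

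| VOCs | No signal | A = 0.70, k = 20 | A = 0.86, k = 10 | A = 0.86, k = 40 |
|---|---|---|---|---|
| 100 | 0.509 / 0.499 / +0.010 | 0.674 / 0.637 / +0.037 | 0.865 / 0.835 / +0.031 | 0.836 / 0.820 / +0.016 |
| 200 | 0.565 / 0.499 / +0.067 | 0.707 / 0.608 / +0.099 | 0.861 / 0.816 / +0.045 | 0.845 / 0.802 / +0.043 |
| 500 | 0.736 / 0.501 / +0.235 | 0.768 / 0.590 / +0.179 | 0.874 / 0.804 / +0.070 | 0.862 / 0.776 / +0.086 |
| 1000 | 0.780 / 0.498 / +0.282 | 0.802 / 0.563 / +0.239 | 0.898 / 0.796 / +0.102 | 0.869 / 0.760 / +0.109 |
| 2000 | 0.811 / 0.503 / +0.308 | 0.825 / 0.550 / +0.276 | 0.902 / 0.780 / +0.121 | 0.879 / 0.737 / +0.142 |

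The Monte Carlo SE of these biases is 0.005 to 0.024. With the screen repeated inside each training fold, bias over the same 20 settings ran from −0.026 (SE 0.013) to +0.016 (SE 0.011), with no consistent direction.

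**Sensitivity to the model and to correlation, screen run once.**
- Fixed-penalty ridge instead of tuned LASSO, independent VOCs, no signal: CV AUC 0.61, 0.68, 0.75 and 0.80 for 100, 200, 500 and 1000 VOCs, against a true 0.50. The small bias at 100 VOCs is thus specific to tuned LASSO.
- Ridge, blocks of 5 VOCs with correlation 0.6: with no signal, CV AUC 0.57, 0.63, 0.70 and 0.75 for the same four counts. With 10 informative VOCs, 0.77, 0.78 and 0.82 against 0.70, 0.67 and 0.65 in new data for 200, 500 and 1000 VOCs, that is +0.07, +0.11 and +0.17.
- Ridge, blocks of 10 with correlation 0.7, attainable AUC 0.86: bias about 0.01, 0.00, 0.02 and 0.02 for 100, 200, 500 and 1000 VOCs. With no signal under such correlation, CV AUC was still 0.51 to 0.70.

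**Scale.** Against the planned SE, 0.070 / 0.016 = 4.4 and 0.142 / 0.016 = 8.9 for the range at 500 to 2000 independent VOCs and attainable AUC 0.86. In the most favourable settings the bias is about one SE or less.

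**The case against.** The strongest reply is that the text never says what the concern needs it to say. It does not state that the screen uses all participants or that it ranks VOCs by association with PDAC; the regressions and the screen are in adjoining paragraphs with no stated link. This stands: both are inferences. They are the natural reading, because the univariate regressions come first, the screen then seeks the most promising VOCs, and its product feeds the models that CV is said to validate.

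Four further points stand in part.
- Nested CV does more than tuning: it also chooses the model to take forward. It still does not cover the screen.
- A second layer of validation is planned, by bootstrap, and its selection routines might include the screen. The text does not say so, and the separate 10-fold CV would remain unprotected. A reader might also infer that the 50% rule is applied after validation; the text places it with the bootstrap and gives no such order.
- The screen is described for the statistical models only. Nothing says that random forest and DNNs start from the screened set.
- Fold-level detail is often left to a statistical analysis plan, which is not shown. But the article does more than omit a detail: it sets an order and says what nested CV is for, and followed as written that leaves the screen outside.

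On size, the plan itself chooses elastic net because VOCs are correlated, and strong correlation with the planned signal nearly removes the bias. That also stands.

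**Conclusion.** The point holds in conditional form. As ordered, the pipeline puts an apparently outcome-driven screen outside the 10-fold CV and does not put it inside the bootstrap. If it is run once on all participants, the CV AUC of the statistical models is biased upward, and so is the bootstrap-corrected AUC if resampling starts from the chosen 50.

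For an assumed 100 to 2000 VOCs, the bias runs from about 0.00 to 0.04 (100 VOCs with tuned LASSO, or strongly correlated VOCs with attainable AUC 0.86) to about 0.07 to 0.14 (500 to 2000 independent VOCs, attainable AUC 0.86). With 500 to 2000 independent VOCs and no signal it is 0.24 to 0.31.

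A reader might infer that the reported performance is bound to be strongly optimistic, or that the study's conclusion could not be supported. The documents do not support that: the number of VOCs, their correlation and the signal are not given, and the plan expects an AUC of 0.86 rather than pure noise.

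Limits of the check: few replicates, simulated Gaussian VOCs, AUC only, and no simulation of the bootstrap-corrected figure, of sensitivity, or of the machine learning models.

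**What to change.** State that the following are repeated from scratch within every outer training fold and every bootstrap resample, with held-out data used for none of them: the univariate screen, the choice of functional form, the top-50 cut, penalty tuning and the 50% selection rule. Keep the choice of model inside the nested loop, as already planned. Apply the same to random forest and DNNs if they use the screened set, and say whether they do. Take headline performance only from that loop.

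Name the ranking criterion and report how many VOCs enter the screen. If the screen is meant to be blind to PDAC status, saying so would remove the problem for that step.

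The cost is a sentence or two in the plan, more computing time and possibly a lower reported AUC. Recruitment and sample collection are unaffected.
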